### 2.2. Selection of Subjects

#### 2.2.1. Participants

Participants who will undergo elective DBS surgery will be informed of the trial before surgery. Interested participants can contact the research coordinator to acquire more information about the study purpose and protocol. The clinical research coordinator will interview potential subjects to assess whether they meet the inclusion and exclusion criteria. Written informed consent will be voluntarily provided by eligible participants to the research coordinator before randomization.

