#### 2.2.2. Inclusion and Exclusion Criteria

Inclusion criteria:Aged ≥ 18;American Society of Anesthesiologists (ASA) physical status of I–III;Able to communicate normally.

Exclusion criteria:Allergy to local anesthetics;Pre-existing infection at block site;Severe coagulopathy;Pre-operative neuropathic pain state;DBS surgery history;Failing to give informed consent or lack of compliance.

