### 2.4. Randomization and Blinding

Patients will be randomly assigned to the SNB group and control group in a ratio of 1:1 using random number tables generated by a computer, including numbers 1–88 which is performed by an anesthesia nurse. The patients corresponding to the first 44 random numbers will be assigned to the control group, while the rest will be allocated to the SNB group. An anesthesia nurse with no direct clinical role in the trial will type the group assignment on separate papers, fold them up, and put them inside sequentially numbered sealed opaque envelopes.

Attending anesthesiologists who are not involved in the follow-up will perform SNB combined with ICNB after the induction of general anesthesia. Participants will be informed as to whether they will receive nerve blocks or not by the research coordinator, who will not participate in treatment or evaluation. Therefore, the attending anesthesiologists, research coordinator, and anesthesia nurse will know the allocation schedule. Group assignment will be concealed from patients, anesthesiologists responsible for operation, and investigators who are in charge of assessing and collecting data. Group allocation will not be disclosed until all data collection is completed. After consultation with the principal investigator (PI), the blinding will be removed if a concern regarding local anesthetic toxicity arises.

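### As written, the coordinator who screens and consents patients also knows the allocation schedule, with no statement that this comes only after enrolment, so concealment is not assured

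*Protocol article*

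**What the plan says.** Section 2.2.1 (Participants) gives the coordinator both steps that decide entry. On eligibility: "The clinical research coordinator will interview potential subjects to assess whether they meet the inclusion and exclusion criteria". On consent: "Written informed consent will be voluntarily provided by eligible participants to the research coordinator before randomization".

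Section 2.4 (Randomization and Blinding) describes a computer-generated list of 88 numbers split 44 and 44: "The patients corresponding to the first 44 random numbers will be assigned to the control group, while the rest will be allocated to the SNB" – that is, to the arm receiving the blocks. The assignments are written out by a nurse without a direct clinical role, who is to "put them inside sequentially numbered sealed opaque envelopes".

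The same section then says: "Participants will be informed as to whether they will receive nerve blocks or not by the research coordinator, who will not participate in treatment or" – the sentence ends by adding evaluation to the excluded tasks. From this it concludes that "the attending anesthesiologists, research coordinator, and anesthesia nurse will know the allocation schedule". The next sentence lists those kept unaware: "Group assignment will be concealed from patients, anesthesiologists responsible for operation, and investigators who are in charge of assessing and collecting data". The coordinator is not on that list.

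**The concern.** Sealed envelopes work only if the person deciding on entry cannot foresee the next assignment. Here that person is named among those who know the schedule. The restriction placed on the coordinator covers treatment and evaluation; it does not cover enrolment.

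There is room for foreknowledge to act. Section 2.2.2 requires that patients can communicate normally and excludes for "Failing to give informed consent or lack of compliance". Both call for judgement, and in a Parkinson's disease population both could plausibly relate to a patient-reported recovery score.

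Selection bias at entry would be hard to detect or repair afterwards. Table 1 schedules QoR-15 only at 24 h, 72 h and 1 month, so there is no preoperative score to compare or adjust for. Section 2.5.4 compares the groups with unadjusted t-tests or Mann-Whitney tests. Masked assessment protects the measurement of the outcome, not the composition of the arms.

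**Working it through.** The defect is procedural and rests on no figure in the plan. The first step matches roles; the others only illustrate what could follow.

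**1. Roles side by side**

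| Task or access | Coordinator | Where stated |
|---|---|---|
| Assesses eligibility | yes | 2.2.1 |
| Receives consent, before randomization | yes | 2.2.1 |
| Knows the allocation schedule | yes | 2.4 |
| Tells participants whether they get blocks | yes | 2.4 |
| Barred from treatment and evaluation | yes | 2.4 |
| Barred from enrolment | not stated | – |
| Listed among those kept unaware | no | 2.4 |
| Learns assignments only after enrolment | not stated | – |

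Section 2.4 also does not say who holds or opens the envelopes.

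**2. Predictability**

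A person who knows the schedule predicts every assignment. A person who knows only past assignments on a single 44/44 list, and always guesses the arm with more places left, is right about 56% of the time (simulation of 20,000 lists), against 50% by chance. So almost all of the exposure comes from access to the schedule, not from the form of the list.

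**3. Illustrative false-positive rates**

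Inputs:
- SD 10.1, from section 2.1.4
- 44 per arm (88 randomized), or 35 per arm (the number section 2.1.4 requires before the 20% dropout allowance)
- no true effect, and an enrolment-driven difference b in expected QoR-15 between the arms; b is an assumption

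Formulas: SE = 10.1 × √(2/n); noncentrality = b/SE; the false-positive rate favouring the block is the probability that a noncentral t with 2n − 2 degrees of freedom exceeds the two-sided 5% critical value.

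- n = 44: SE = 10.1 × √(2/44) = 2.153, 86 df, critical value 1.988
- n = 35: SE = 10.1 × √(2/35) = 2.414, 68 df, critical value 1.995

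| Assumed b (points) | Noncentrality, n = 44 | Rate, n = 44 | Noncentrality, n = 35 | Rate, n = 35 |
|---|---|---|---|---|
| 0 | 0 | 2.5% | 0 | 2.5% |
| 1 | 0.464 | 6.7% | 0.414 | 6.0% |
| 2 | 0.929 | 14.9% | 0.828 | 12.6% |
| 3 | 1.393 | 28.0% | 1.243 | 23.1% |

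**4. How much steering such a gap would need**

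Suppose the coordinator's impression correlates ρ with the 24 h score (an assumption), and a fraction q of candidates is turned away in each arm, in opposite directions. The gap is 2 × ρ × 10.1 × φ(z)/(1 − q), where φ is the standard normal density and z the normal quantile of q. With ρ = 0.5 and q = 0.10: 2 × 0.5 × 10.1 × 0.1755/0.90 = 1.97 points. For ρ between 0.5 and 0.3, a 2-point gap needs q of about 10% to 19%, and a 3-point gap about 16% to 30%.

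**The case against.** The strongest reply is that the sentence on the schedule draws a conclusion. It begins with a word of inference and follows the sentences saying that attending anesthesiologists perform the blocks and that the coordinator informs participants. In context it can be read as a list of roles that become unblinded once a patient has been assigned. Sealing the envelopes makes little sense if the enroller is meant to hold the list, and consent is placed before randomization. On that reading concealment is largely intact, apart from the slight predictability of one 44/44 list.

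This reading is possible, and it rules out the stronger inference that a reader might draw: that allocation is definitely unconcealed, or that enrolment has been steered. The documents support neither. But the text speaks of the schedule, not of single assignments, gives no timing, and grants this knowledge to the role that enrols. Custody of envelopes may be left to a fuller document; a positive statement that the enroller knows the schedule is a different matter.

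It is also fair to object that the illustrative imbalances have no source in the documents and that the larger ones would need sustained selection of candidates, as step 4 shows. That stands. The percentages show sensitivity and are not an estimate of bias in this trial.

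**Conclusion.** The point holds in this form: the article does not establish that the person who judges eligibility and takes consent is unaware of upcoming assignments, and its wording says the reverse. Followed literally, it removes the protection that the envelopes are meant to give. Whether concealment fails in practice depends on when the coordinator learns assignments, which the article does not say.

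The size is unknown. Under the assumptions in step 3, imbalances of 1 to 3 points would raise the rate of false positives favouring the block from 2.5% to between about 7% and 28% at 44 per arm, or between about 6% and 23% at 35 per arm. Because a failure of concealment cannot be reliably undone in the analysis, the passages should be reconciled even though the milder reading may be the intended one.

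A related contradiction is clear on any reading: section 2.4 has the coordinator tell participants whether they will receive blocks, and then says that assignment is concealed from patients.

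**What to change.** Amend section 2.4, and Table 1 to match:

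- State that only the nurse who generates the list and prepares the envelopes holds the schedule, and remove the research coordinator from those who know it.
- Delete the sentence in which the coordinator informs participants whether they will receive blocks. It is the apparent reason for the coordinator's access, and it contradicts concealment from patients.
- Have the anesthesiologist who performs the blocks open the next numbered envelope only after eligibility and consent are recorded, so that this person learns one assignment at a time.
- Align the timing of allocation in Table 1, which now places it before induction, with the moment the envelope is opened.
- Section 2.1.4 says the trial began in April 2022. For patients already enrolled, report who had access to the schedule and when, since new wording cannot protect them retrospectively.

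The cost is a small change of wording and access. It needs no extra staff, because the nurse, the envelopes and the blocking anesthesiologist are already in the plan.

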### 2.5. Data Collection and Analysis

#### 2.5.1. Data Collection and Management

Researchers will explain the advantages of participating in the study to participants and their authorized surrogates before DBS surgery. A specific masked researcher will collect the patients’ basic characteristics before surgery. After the surgery, the blinded investigator will conduct a follow-up to record QoR-15 scores at 24 h and 72 h after surgery in the ward, and at 1 month after surgery in the outpatient clinic. Participants will be excluded if they are unable to complete the primary outcome measure. The anesthesiologists in charge will record the patients’ intraoperative data. Other data on secondary outcomes will be collected by a blinded investigator. The data collected will be first completed on a paper Case Report Form (CRF). Following this, the data manager will merge the double data into an electric database which will be examined by two inspectors.

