#### 2.1.1. Primary Outcome

The study’s primary outcome is the scores of QoR-15 at 24 h after surgery.

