#### 2.1.3. Outcome Measures

The QoR-15 questionnaire will be used to measure the patients’ quality of recovery at 24 h, 72 h, and 1 month after operation. A higher QoR-15 score (from 0 to 150) suggests greater recovery after surgery. The NRS score will be used to measure postoperative pain, and a higher score indicates more severe pain after surgery. The NRS scores will be recorded before discharge from PACU at 24 h, 72 h, and 1 month following surgery. Neuropathic pain will be assessed before surgery by a modified Douleur Neuropathique 4 (DN4) questionnaire on a scale of 0–10. A total DN4 score of more than or equal to 4 indicates neuropathic pain.

Emergence agitation is identified as improper behavior that presents itself as excitation, agitation, and concurrent orientation disorder during the anesthesia recovery phase. Respiratory recovery time refers to the interval between the end of anesthetic drugs and respiratory recovery. Response time is defined as the interval between the cessation of anesthetic drugs and response to a verbal command. Duration of time between the cessation of anesthetic drugs and extubation is referred to as the extubation time.

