#### 2.1.4. Sample Size and Recruitment

The study’s primary outcome is the scores of QoR-15 at 24 h after surgery. Our preliminary study showed that the scores of QoR-15 at 24 h following DBS operation in PD patients without nerve block were equivalent to 110 (10.1). A previous study has shown that the QoR-15 score change of 8 points was deemed to be a clinically significant difference [26]. We calculated the required number of patients using PASS 11 software (NCSS, Kaysville, UT, USA) with an alpha error of 0.05 and power 95% (test for two proportions, two-sided *t*-test), and determined that 35 patients would need to be included in each group. Considering a 20% dropout rate, we defined a sample size of 88 participants.

Recruitment will be performed during a 12-month period. The study will end when the last patient enrolled undergoes an assessment of QoR 1 month after surgery. The protocol has been initiated as planned in April 2022 and will be completed in March 2023.

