#### 2.3.2. Criteria for Termination or Adjusting the Assigned Interventions

There will be no unique criteria for changing assigned interventions, but there are situations under which the research will be terminated: (1) postoperative surgical site bleeding; (2) serious DBS surgery-related complications (such as pulmonary aspiration, wound infection, respiratory insufficiency, and delirium) and nerve-block-related AEs (such as pneumothorax and local anesthetic toxicity); (3) unexpected postoperative continuation of intubation; and (4) unanticipated reoperation 24 h following surgery.

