#### 2.5.4. Statistical Analysis

Masked statistical analysts will conduct the analyses at the Clinical Research Center of Changhai Hospital. The full analysis set including all randomized patients and per protocol set, including patients with the primary outcome, will be performed. Safety and efficacy analyses will be conducted based on the intention-to-treat analysis population, which includes all randomized patients. Missing data will be handled using the mixed model for repeated measurements.

All statistical analysis will be performed by SPSS 23.0 statistical analysis software (IBM SPSS, Armonk, NY, USA). Continuous variables in normally distributed data represented as mean (SD) will be compared using the Student’s t-test, while continuous variables in non-normal distribution data reported as medians (quartiles) will be compared using Mann-Whitney *u* test. Categorical variables described as frequency and percentages will be compared using χ^2^ test or Fisher’s exact test. *p* < 0.05 will be regarded as statistically significant.

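### The protocol excludes randomised patients who cannot complete the 24 h QoR-15, yet promises an analysis of everyone randomised: the two rules conflict for exactly these patients

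*Protocol article*

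**What the plan says.** Section 2.1.1 fixes the endpoint: "The study’s primary outcome is the scores of QoR-15 at 24 h after surgery". The scale runs from 0 to 150 and higher is better (section 2.1.3). Table 1 schedules the QoR-15 at 24 h, 72 h and 1 month, with no preoperative score.

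Section 2.5.1 describes these follow-up contacts and then says: "Participants will be excluded if they are unable to complete the primary outcome measure".

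Section 2.5.4 introduces two analysis sets: "The full analysis set including all randomized patients and per protocol set, including patients with the primary outcome, will be performed". It continues: "Safety and efficacy analyses will be conducted based on the intention-to-treat analysis population, which includes all randomized patients". On incomplete data it says: "Missing data will be handled using the mixed model for repeated measurements". The same section then names the Student's t-test or the Mann-Whitney test for continuous variables.

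Section 2.3.2 lists events that end participation. They include surgical-site bleeding, delirium, respiratory insufficiency, continued intubation, reoperation, and the block-related events pneumothorax and local anaesthetic toxicity.

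**The concern.** Both rules are stated, and they give opposite answers for the same patient. This is not a detail left to an analysis plan that is not shown, because the conflict lies within the article.

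Who enters the primary comparison is at stake. The QoR-15 is patient-reported, so a patient who is delirious, still intubated or back in theatre at 24 h may be unable to answer, and those states are themselves poor recovery. Excluding such patients makes the comparison conditional on being well enough to answer. Randomisation does not protect that comparison if the arms lose different numbers or different kinds of patients. Control patients receive no block (section 2.3.1), so pneumothorax or local anaesthetic toxicity from the block can occur in one arm only. Balanced exclusion therefore cannot be taken for granted.

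**Working it through.** **Step 1: the rules side by side, for a randomised patient with no 24 h QoR-15.**

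| Source | Status of this patient |
|---|---|
| Section 2.5.1, exclusion sentence | Out, with no analysis set named |
| Section 2.5.4, full analysis set and intention-to-treat population | In |
| Section 2.5.4, per protocol set | Out |
| Section 2.5.4, mixed model for missing data | In, with the missing score handled by the model |

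The exclusion sentence reproduces the per protocol set and contradicts the other two rules. Once it is applied, no 24 h score is missing. The model could still meet missing 72 h and 1-month scores.

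**Step 2: the plan's own figures.** The article gives no expected number of patients unable to answer at 24 h. The nearest figure is the 20% dropout allowance in section 2.1.4, and that step reproduces: 2 × 35 = 70, and 70 / (1 − 0.20) = 87.5, rounded up to 88. It is a general allowance and is not used below as an exclusion rate. The 35 per group does not follow from the stated inputs (8 points, SD 10.1, two-sided 0.05, 95% power), which give 42 per group by the normal approximation and 43 by the t-test. That is a separate matter, and nothing here depends on it.

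**Step 3: shift per excluded patient.** Take an arm of 44 (88 / 2) with m patients excluded, whose scores would average G points below the completers' mean.

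- All-patient mean = completers' mean − (m/44) × G.
- Exclusion therefore raises the arm mean by (m/44) × G.
- With the same G in both arms, the difference (SNB minus control) shifts by (k/44) × G, where k is SNB exclusions minus control exclusions.

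G is not in the documents. I assume 20 to 40 points.

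| Net extra exclusions in one arm | G = 20 | G = 30 | G = 40 |
|---|---|---|---|
| 1 | 0.45 | 0.68 | 0.91 |
| 2 | 0.91 | 1.36 | 1.82 |
| 4 | 1.82 | 2.73 | 3.64 |

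The shift favours SNB if the SNB arm loses more patients and favours control if the control arm does. If k = 0 it is zero. At G = 30, two net exclusions are 1.36 / 8 = 17% of the target difference and four are 2.73 / 8 = 34%.

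**Step 4: cross-check with a different model.** Assume normal scores with SD 10.1 (section 2.1.4) and a true difference of 8, and suppose that the lowest-scoring fraction f of an arm cannot answer. The completers' mean is then μ + 10.1 × φ(z_f) / (1 − f), where z_f is the normal quantile at f.

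- f = 15%: 10.1 × 0.2332 / 0.85 = 2.77 points upward.
- f = 5%: 10.1 × 0.1031 / 0.95 = 1.10 points upward.
- 15% control and 5% SNB: 8 − 1.67 = 6.3.
- 5% control and 15% SNB: 8 + 1.67 = 9.7.
- Equal fractions: 8.0.
- One common score threshold that removes 10% overall (16.2% of control, 3.8% of SNB): 5.9.

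**Step 5: how plausible is G?** In this model the gap between excluded patients and completers is 10.1 × φ(z_f) / (f(1 − f)): 21.9 points at f = 5% and 19.7 at f = 10%. This sits near the low end of the assumed range. Gaps of 30 or 40 need excluded patients to lie well outside the distribution seen in the preliminary study.

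**The case against.** The best defence is that the sentence in section 2.5.1 is only loose wording for the per protocol set. Section 2.5.4 defines that set as patients with the primary outcome, and it is the statistical section that assigns efficacy and safety to everyone randomised. This reading is plausible. It means that a complete-case primary analysis is not settled, although a reader might infer that it is. But section 2.5.1 does not mention the per protocol set, and staff collecting data could apply the sentence as it stands. Under either reading the text needs correction.

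Other parts of the defence stand and limit the point:

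- A reader might infer that the worst recoveries will be dropped. The article does not say so. Section 2.3.2 makes it plausible, but some patients will fail to answer for unrelated reasons.
- A reader might infer that the mixed model is left with nothing to do. That holds only for the 24 h score.
- A reader might infer that later scores and adverse events of excluded patients are lost. Section 2.5.1 does not say that follow-up stops, Table 1 schedules adverse events to 1 month, and section 2.5.4 analyses safety in everyone randomised. These data are at risk only if exclusion is taken to end follow-up.
- A reader might take the 20% allowance as the number to be excluded. It covers dropout in general, whereas the 24 h score is collected in the ward.

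Keeping patients in a mixed model is also not a complete cure. The model assumes data missing at random. If inability to answer depends on the unseen 24 h score, bias remains. With no preoperative QoR-15, a patient who has no score at any visit adds no outcome information.

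**Conclusion.** The contradiction is certain from the text. It should be resolved before analysis, and preferably while follow-up can still be secured, because it decides who is in the primary comparison.

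The bias is conditional. It requires that inability to answer is related to recovery and that the arms differ in how many, or how severely affected, patients are excluded. Its direction is not fixed. It is near zero if equal fractions with similar deficits are excluded. Under an assumed deficit of 20 to 40 points it is about 0.5 to 0.9 points per net extra exclusion in an arm of 44, and the normal model points to the lower end of that range. Nothing in the article predicts the size of any imbalance, so the larger totals in the working illustrate what could happen and are not forecasts.

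**What to change.** 1. Delete the exclusion sentence in section 2.5.1, or confine it expressly to the per protocol set.
2. State that randomised patients without a 24 h QoR-15 stay in the trial and in the primary all-randomised analysis, that their 72 h, 1-month and adverse-event data are still collected, and that the reason for the missing score is recorded and reported by arm. Reconcile this wording with the list in section 2.3.2, on which no view is taken here.
3. In section 2.5.4, name the mixed model, fitted to the 24 h, 72 h and 1-month scores, as the primary analysis of the 24 h difference. At present the section names this model for missing data and a t-test or Mann-Whitney test for the comparison.
4. Add one sensitivity analysis that does not assume data missing at random, for example a low score, fixed before unblinding, for patients too unwell to answer.

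The cost is revised wording and one extra analysis. The follow-up visits are already scheduled, and recording the reason for a missing score adds one item to the case report form.
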